# STUDY PROTOCOL: EXPOSURE IN VIRTUAL REALITY FOR SOCIAL ANXIETY DISORDER - a randomized controlled superiority trial comparing cognitive behavioral therapy with virtual reality based exposure to cognitive behavioral therapy with in vivo exposure

**DOI:** 10.1186/s12888-020-2453-4

**Published:** 2020-01-30

**Keywords:** Social anxiety, Virtual reality, Cognitive behavioral therapy, Exposure

## Abstract

**Background:**

Social Anxiety Disorder (SAD) is characterized by an intense fear of negative judgement by others. Cognitive Behavioral Therapy (CBT) is recommended for treatment, but a substantial part of individuals with SAD either do not seek treatment or drop-out. CBT with Virtual Reality (VR)-based exposure has several advantages compared to traditional exposure methods, mainly due to increased control of situational elements. The aim of the current study is to develop a CBT program containing VR-based exposure. The intervention is targeted to adult patients suffering from SAD and treatment effect will be assessed by changes in SAD symptoms.

**Methods:**

This article describes the study protocol of a Randomized Controlled Trial with three arms: 1) CBT with VR exposure based on 360° videos 2) CBT with in vivo exposure and 3) VR relaxation therapy. There will be 30 participants in each arm with a crossover at the end of the treatment period during which the participants in the third group will be randomly re-allocated to one of the two former groups. The treatment program consists of 10 weekly individual sessions with a psychologist, and a six month follow-up consisting of a questionnaire. The primary outcome measure is reduction in SAD symptoms which will be assessed with the Social Interaction Anxiety Scale (SIAS).

**Discussion:**

There are currently no published studies on CBT with VR exposure based on 360° videos for SAD treatment. Furthermore, the current study will be the first Danish SAD treatment program that includes VR technology.

**Trial registration:**

clinicaltrials.gov (NCT03973541) June 3rd 2019.

## Background

Social Anxiety Disorder (SAD) is a common yet underreported mental disorder with an estimated lifetime prevalence of 3–13% [1–3], and low rates of spontaneous remission [4]. Patients with SAD experience intense and persistent fear during social interactions, where he or she might be negatively evaluated by others (e.g. public speaking, shopping). Symptoms include a high degree of bodily symptoms, such as sweating, trembling and increased heart rate, causing avoidance behavior when exposed to social situations (e.g. education, work) and significant functional impairment [5]. SAD is therefore highly debilitating, and the majority of individuals with social anxiety reports numerous problems with individual and social adjustments, as well as impairment in academic and professional functioning [6].

SAD often co-occurs with other psychiatric conditions such as additional mood disorders, substance use disorders, and is significantly associated with suicidal ideation [7, 8]. Despite its frequency and severity, only between one third and half of people with SAD seek treatment [5, 9]. This may be linked to the nature of the disorder itself, as people with SAD avoid healthcare services like they would any other social interaction [7]. Factors such as embarrassment associated with help-seeking and fear of what others might think have been found to prevent individuals with SAD from seeking treatment [7]. In addition to the disorder-specific issues, futher barriers exists in regards to accessing treatment such as the lack of skilled therapists, lack of evidence-based treatments and long waiting lists [10]..

The recommended psychological treatment for SAD is the exposure technique imbedded in Cognitive Behavioral Therapy (CBT) [2, 5]. CBT for SAD combines cognitive restructuring with exposure [11]. In exposure-based therapy, exposures to social situations are used to test and disprove the patient’s predictions about the danger in a particular situation thereby developing new, realistic mental representations associated with the feared stimuli [12, 13]. Patients with SAD often have excessively high standards for social performance, and a strong fear of ridicule [12, 14]. Thus, it can be particularly helpful to encourage patients to behave in ways that they would consider unacceptable. i.e. intentionally acts against their excessively rigid rules for social interaction while observing the consequences [12, 14].

Exposure has traditionally taken place as either.
In vivo: directly facing the feared situation.Imaginary exposure: imagining the feared situation (can be facilitated through pictures or videos).

In vivo exposure is effective [14] but is costly, time-consuming and situational elements, such as the reaction of others, are difficult to control [15, 16]. Furthermore, many patients are rather unwilling to expose themselves to the real situation since it is considered too frightening [17], and there is a risk of encountering familiar people revealing that the person is in therapy.

Conversely, imaginary exposure may lack realism and intensity [18], and can be difficult for people who are unable to imagine vividly, it is also easy to avoid imagining their phobia-inducing situations, or for the patient to overwhelm themselves with images [17, 19]. Recently, researchers and clinicians have started to use Virtual Reality (VR) to overcome these difficulties [15, 16].

### Virtual reality- based exposure

VR is the use of computer and behavioral interfaces to simulate the behavior of 3D entities that interact in real time with each other and with a user immersed via sensorimotor channels [20]. It immerses the user in a computer generated or video-based virtual environment [21] . This enviroment can be created using either computer graphics or 360° 3D videos [21–23]. Studies on the effect of VR-based treatment for different types of phobias (e.g. agoraphobia and fear of flying) have revealed great potential [21], and a study showed that 76% of participants preferred VR-based exposure over in vivo exposure [24]. In addition to high levels of preference, VR-based exposure does have several advantages:

Virtual exposure scenarios can be very similar to real life situations [25], and it is possible to control and regulate situational factors, such as degree of exposure for the patient and the reactions of other people in the scenario [26].Exposure scenarios can be presented to the patients, while still in the comfort and safety of a therapeutic room [25],The flexibility of VR allows the patient to experience situations that are worse and more exaggerated than those that are likely to be encountered in real life [17]. Thus it is possible to expose patients to others’ negative reactions, in a safe environment where they can learn that this is not dangerous, and that they can handle even the social ridicule they fear the most.Patients know that it is not real but their minds and bodies behave as if it is real. Hence people will more easily face difficult situations in VR than in real life and be able to engage in more adaptive behaviors [27].VR sessions often requires less time than in vivo sessions, and can be planned more flexibly and for less costs [28]

Seven meta-analyzes [9, 29–34] have been published on CBT with VR-based exposure for anxiety, and six of these include studies on SAD [9, 29–31, 33, 34]. All found superior effect of CBT with VR-based exposure compared to imaginary exposure, and similar effects when compared to in vivo exposure, with a recent study finding superior effect of CBT with VR-based exposure even when compared to in vivo [28]. Treatment effects have been shown to persist over a number of years [27], and a recent meta-analysis found persistent benefits of treatment after CBT with VR-based exposure comparableto face-to-face therapy [17]. Furthermore, a meta-analysis found that the CBT with VR-based exposure promoted benefits which carry over to real life, and leads to significant behavior change in real-life situations, [32] this analysis however, did not include SAD specific studies [32].

These meta-analyzes include only five [28, 35–38] randomized controlled trials (RCTs) on VR-based treatment for SAD which, however, all found significant improvements in SAD after VR-based treatment. Regarding the individual studies, one study comparing VR exposure with a waitlist group found a significant higher improvement in measures of anxiety in the VR exposure group [35]. Two studies found no significant difference between VR-based and in vivo exposure [36, 37], and Bouchard et al. (2017) [28] found VR exposure to be superior to in vivo exposure, whereas Kampmann et al. (2016) [38] found that in vivo exposure without CBT was more effective than VR-based exposure without CBT. However, as exposure was not performed in the context of CBT, direct comparison to the other studies is not possible.

The current evidence thus supports the clinical efficacy of CBT with VR-based exposure, and it is suggested that if the potential of VR is fully explored it might be more effective than in vivo [28]. However, the fact that these meta-analyzes include a total of only six [28, 35–39] (RCTs) and only four of these compare CBT with VR-based exposure to both an in vivo and a control group [28, 37–39]. The strength of the evidence base is also weakened by the use of small sample sizes (*n* < 30) [29] [32, 40] and the use of waiting lists patients as control groups [41], as waiting list control designs may overestimate intervention effects [42]. Patients assigned to a waiting list appear to improve less than would be expected for people who are concerned about their behavior and are taking steps to change. This contrasts with studies not employing waiting list designs in which control group patients tend to improve [43].

So far, CBT with VR-based exposure for SAD has been conducted by the use of computer-generated social environments. This method requires the computer to recreate (render) in real time all the virtual stimuli in order to adapt the user’s movements and interactions with the virtual stimuli. The advantage of real time 3D rendering is that the user can explore the virtual environment at will and at his her or her own pace. The disadvantages it that it takes computer power and time, and all stimuli has to be synthetic (digitized). Also, it is difficult and expensive to develop [44]. Using 360° videos avoids some limitations of real time rendering of 3D stimuli as it is more realistic, less expensive and requires minimal training, and developers can use real stimuli. All this contributes to making it easier to implement. However, the user cannot fully explore the environment (i.e., cannot go in directions that were not filmed in the video) or at his or her own pace (i.e., event will occur as already planned and filmed in the video). Video-based CBT with VR-based exposure has not yet been applied to SAD, but a study on social anxiety in the context of psychosis revealed positive results [45].

In 2017 Centre for Telepsychiatry did a pilot study (manuscript submitted) investigating the ability of 360° videos to trigger an anxiety response in patients with SAD. We developed and produced three videos in a shopping center and tested them on nine SAD patients and nine matched controls. Our main finding was that the videos were effective in producing anxiety in SAD patients while the control group did not report any anxiety. Furthermore, the participants reported high levels of presence. Presence is the person’s subjective sensation of being there in the Virtual Environment (VE) and appears to be key when inducing emotions such as anxiety through technology [46].

### Aims and hypotheses

The aims of the study that will use the clinical protocol described in the paper are to develop a complete program of CBT with VR exposure based on 360° videos for adult patients suffering from SAD, and to evaluate the treatment effect on SAD symptoms. We plan to compare a group receiving CBT with VR-based exposure immersed in an environment based on 360 videos stimuli to a group receiving CBT with in vivo exposure and a group receiving VR relaxation treatment. Having VR relaxation treatment as control group is methodologically superior to a comparison to a waiting list and controls for any placebo effect.

It is hypothesized that:
CBT with VR-based exposure will significantly reduce symptoms of SADCBT with VR-based exposure will be more effective than both CBT with in vivo exposure and VR relaxation therapy at the end of treatmentAn effect on symptom reduction will sustain at 6 months follow-up

## Methods

### Design

The study is designed as a three arm randomized controlled trial comparing a group receiving CBT with VR-based exposure, a group receiving CBT with in vivo exposure and a group receiving VR relaxation.

### Participants and recruitment

Patients have to meet the following criteria:

#### Inclusion criteria

Able to comprehend the Danish language.≥18 years.Fulfill the diagnostic criteria for SAD according to ICD-10 (F40.1) or ICD-11 (6B04).

#### Exclusion criteria

Previously diagnosed with psychosis, Autism Spectrum Disorder or severe depression.Participating in other psychotherapeutic treatments during the study.Substance dependence disorder.Severe cyber-sickness (corresponding to motion sickness).If on medication, medication must be stable for 6 months prior to the study and during the study (i.e., no changes in type of medication or dosage).

Patients are recruited from the mental health services in the Region of Southern Denmark and from the Internet clinic at the Centre for Telepsychiatry (CTP). Patients are also recruited from the job centers in this Danish region. Case managers in these centers have in some cases experienced difficulties in getting people hired due to psychological problems and specifically due to what might be SAD. Most case managers have an educational background as social workers and have received basic knowledge on mental health as part of their education. They will be further trained by the research leader to identify job seekers who have difficulties getting a job due to problems that might have its cause in SAD. The case managers will hand out written information material to potential patients. Furthermore, we will advertise on the homepages for the CTP, for the Region of Southern Denmark, and at a national health website sundhed.dk

Participants will receive written information material and be asked to complete an online version of the Social Interaction Anxiety Scale (SIAS) [47]. If the SAD patient meets the inclusion criteria they are invited to a meeting conducted either at the CTP or through video call for oral information and diagnostic assessment. All potential participants will have their diagnoses discussed at weekly clinical conference. Those who meet the inclusion criteria will be offered participation and be asked to sign an informed consent statement.

Study data will be collected and managed using the Research Electronic Data Capture (REDCap) tools [48] hosted at the mental health services in the Region of Southern Denmark. REDCap is a secure, state-of-the-art web-based application designed to support data capture for research studies.

### Randomization and blinding

Patients are randomly assigned (by gender, age and baseline severity of SAD) to one of the following three arms in ratio 1:1:1 via the computerized randomization function in REDCap: 1) Individual CBT with VR-based exposure in session 2) Individual CBT with in vivo exposure in session or 3) Individual VR relaxation therapy. Assignment will be kept blind for patients and clinicians until the first exposure session. An equal number of patients will be assigned to each group, but at the end of treatment patients in the third group will be randomly re-allocated to one of the two former groups. This reallocation is done to reduce the total number of patients needed to be recruited, and to avoid the ethical problem of not offering effective treatment. Six months after end of treatment the patients in group 1 and 2 will be re-assessed. There will not be a follow-up assessment of the patients in group 3, as they are re-allocated after week 10 (see Fig. 1).

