### Sample size

Previous studies [28] report an approximately 10 point drop in SIAS for standard treatment with in vivo exposure. However, a 20 point drop has been observed for CBT with VR-based exposure [28] with standard deviations around 15 points in all treatment groups. We calculated effect sizes and found that 38 subjects are required in each group to detect if VR treatment is significantly better than standard treatment with in vivo exposure in a t-test with 80% power at the 0.05 significance level using a two-sided hypothesis. However, patients in the VR relaxation group continues in one of the exposure groups, so only 76 subjects need to be recruited. To compensate for a possible 10% drop-out rate we plan to recruit 90 patients.

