### Statistical methods

The effect of the treatment will be analyzed using a linear mixed effects (LME) model with the SIAS score as the outcome and treatment group and assessment point (baseline, before exposure sessions, post-treatment and six months follow-up) as the independent variables, allowing intercepts to vary between patients. The moderating effect of ADHD symptoms severity, autism spectrum characteristics, depressive symptoms, alcohol and drug use on the treatment outcome will be investigated by including them as covariates in the regression. Comparisons for the SWEAT will be performed with t-tests, set two-tailed.

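### Assignment is balanced on gender, age and baseline severity, but the stated model omits gender and age and does not say that baseline SIAS is adjusted for, so precision may be lost

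*Protocol article*

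**What the plan says.** Protocol article, Randomization and blinding: "Patients are randomly assigned (by gender, age and baseline severity of SAD) to one of the following three arms". Allocation is equal across the arms and generated in REDCap. The method of balancing and any cut-points for age or severity are not given.

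Protocol article, Statistical methods: the effect is estimated with a "linear mixed effects (LME) model with the SIAS score as the outcome and treatment group and assessment point" as predictors. The assessment points are "baseline, before exposure sessions, post-treatment and six months follow-up) as the independent variables, allowing intercepts to vary between patients". Baseline SIAS is therefore one of four outcome levels. The section states neither a group-by-assessment-point term nor a common baseline mean across arms. The other covariates named serve a different purpose: "The moderating effect of ADHD symptoms severity, autism spectrum characteristics, depressive symptoms, alcohol and drug use on the treatment outcome". Gender and age do not appear in the section.

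Protocol article, Sample size: the VR exposure versus in vivo comparison rests on an "approximately 10 point drop in SIAS for standard treatment with in vivo exposure" against "a 20 point drop has been observed for CBT with VR-based exposure", with a standard deviation of about 15. It uses a two-sided t-test at 0.05 with 80% power, giving 38 per group. The article does not say whether 15 is the SD of the score or of the change.

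**The concern.** Variables important enough to balance the arms on are normally carried into the analysis. Balancing on a prognostic factor lowers the true variance of the treatment contrast. A model without that factor does not credit the gain, and its standard error tends to be too wide.

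Baseline SIAS matters most here, as it is the baseline value of the outcome itself. If baseline is modelled as an outcome and each arm keeps its own baseline mean, the post-treatment contrast is in effect a comparison of change scores. That is less precise than a baseline-adjusted comparison whenever the baseline to post-treatment correlation is below 1.

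What is at stake is power. The abstract plans 30 patients per arm, and 38 per group for VR exposure versus in vivo is reached only by adding re-allocated relaxation patients.

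**Working it through.** **Inputs from the article.** Difference 20 − 10 = 10 points; SD 15; two-sided alpha 0.05; 38 per group; 30 per arm as randomised; 10% drop-out, so 30 × 0.9 = 27 per arm.

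**Assumptions, not in the article.** Baseline to post-treatment correlation rho of 0.3, 0.5 and 0.7. Variance explained by gender and age of 0 to 10%.

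**1. The plan's own figure.** Normal approximation: n = 2 × (1.960 + 0.842)² × 15²/10² = 35.3, so 36 per group. The exact t calculation gives 37. The stated 38 is reproduced to within two patients, and power at 38 is 0.82 (t-test).

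**2. Variance of the contrast.** Let SD be the standard deviation of the score, equal at both times. Per-patient variance is:

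- group-by-assessment-point contrast, unconstrained baseline means: 2 × SD² × (1 − rho)
- adjusted for baseline, or with baseline means constrained equal: SD² × (1 − rho²)

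The ratio of unadjusted to adjusted variance is 2(1 − rho)/(1 − rho²) = 2/(1 + rho), which is 1.54, 1.33 and 1.18 at rho 0.3, 0.5 and 0.7.

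The standard errors of a random-intercept model with four assessment points, 38 per arm and score SD 15 agree. Unconstrained versus constrained baseline gives 4.07 versus 3.28, 3.44 versus 2.98 and 2.67 versus 2.46 points at the same three correlations.

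**3. Power at 27 per arm, 10-point difference, two-sided t-test.**

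If 15 is the SD of the score, the effective SD is 15√(2(1 − rho)) unadjusted and 15√(1 − rho²) adjusted:

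| rho | SD unadjusted | SD adjusted | power unadjusted | power adjusted |
|---|---|---|---|---|
| 0.3 | 17.75 | 14.31 | 0.53 | 0.71 |
| 0.5 | 15.00 | 12.99 | 0.67 | 0.79 |
| 0.7 | 11.62 | 10.71 | 0.87 | 0.92 |

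If 15 is the SD of the change, the unadjusted SD is 15 at every rho and the adjusted SD is 15√((1 + rho)/2):

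| rho | SD adjusted | power unadjusted | power adjusted |
|---|---|---|---|
| 0.3 | 12.09 | 0.67 | 0.85 |
| 0.5 | 12.99 | 0.67 | 0.79 |
| 0.7 | 13.83 | 0.67 | 0.74 |

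**4. Power at the planned 38 per group.** At rho 0.5 the two readings of SD 15 coincide, and power rises from 0.82 to 0.91.

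**5. Gender and age.** If they explain a share R² of the variance of the contrast, omitting them widens the standard error by 1/√(1 − R²): 1.00 at 0%, 1.03 at 5% and 1.05 at 10%. With SD 15 and no other adjustment, the n needed for 80% power goes from 37 to 35 to 33 per group. Any effect of gender or age that is constant over time cancels in a change-type contrast, so only their relation to change counts. That is why the range must include zero.

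**The case against.** The strongest objection is that the loss from the baseline part depends on a parameterisation that the article does not state. Treating baseline as an outcome level is not a defect in itself. With a random patient intercept and a common baseline mean, the precision equals that of baseline adjustment and nothing is lost. This stands, and it makes the baseline part conditional.

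It can also be said that a condensed article leaves adjustment terms to a fuller document, and that the five named covariates are moderators, not an adjustment set. This stands in part: a fuller document may add the terms. But the article does list the model's independent variables and its random effect, and that list omits two of the factors it balances on.

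A reader might infer more than the text supports:

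- That the treatment estimate is biased or the test invalid. Omitting balancing factors leaves the estimate unbiased, and the standard errors are, if anything, conservative.
- That the sample size is wrong. It was sized on an unadjusted t-test, and 38 per group reproduces without any adjustment.
- That the trial is underpowered for this reason. At 38 per group and rho 0.5, even the unadjusted contrast has power 0.82. The lower figures belong to 27 per arm.
- That randomisation is stratified. The article says only that assignment is by these factors; the method could be stratification or minimisation. The case for analysing the factors is the same either way.

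**Conclusion.** The mismatch between the assignment factors and the stated model is real, and its consequence is efficiency, not validity. Gender and age are left out of the model, and the text does not secure the precision available from baseline SIAS.

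The size of the baseline part rests on three things that the article does not settle: that the effect is read from a group-by-assessment-point contrast with unconstrained baseline means, the value of rho, and the meaning of SD 15. Under that contrast the direction is the same for every rho below 1. Over rho 0.3 to 0.7 at 27 per arm, the gain in power is 0.05 to 0.18 if 15 is the SD of the score (0.92 − 0.87 to 0.71 − 0.53). It is 0.07 to 0.18 if 15 is the SD of the change (0.74 − 0.67 to 0.85 − 0.67). At 38 per group and rho 0.5 it is 0.09. With a common baseline mean it is zero.

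The gender and age part is probably small and may be close to nothing. The change is worth making because it is nearly free.

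**What to change.** In Statistical methods, state that the treatment effect is the group contrast at post-treatment. Estimate it with baseline SIAS as a covariate for the post-baseline scores or, equivalently in precision, with baseline kept as an outcome and its mean constrained equal across arms. Add gender and age. Cross each covariate with assessment point, so that it acts on the post-treatment contrast and does not merely shift the overall level.

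The cost is a few degrees of freedom and a change of wording. All the variables are used for assignment and so are already known at randomisation; no new data, visits or patients are needed. Fixing the wording before the analysis also removes a later choice between adjusted and unadjusted results.
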